**Methods:**

This is a randomized, double-blinded, double-dummy, parallel, positively controlled, adaptive, multicenter clinical trial. All participants will be randomly allocated by a central randomization system to the treatment group or the control group in a 1:1 ratio. The treatment group will undergo a 14-day treatment with Bushen Culuan Decoction 13 g three times a day and a 5-day treatment with clomiphene citrate placebo tablets 50 mg once a day starting on day 5 of every menstrual period. The control group will undergo a 14-day treatment with Bushen Culuan Decoction placebo 13 g three times a day and a 5-day treatment with clomiphene citrate tablets 50 mg once a day from day 5 in every menstrual period. The whole treatment will last through 3 menstrual periods or 6 menstrual periods, depending on whether ovulation is regained in the first 3 menstrual periods. All statistical analyses will be performed in SPSS 21.0 (SPSS, Chicago, Illinois, USA), and a *p* value < 0.05 will be considered statistically significant.

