### Sample size estimation

In a previous study, the total effective rate (Total effective rate% = (markedly effective + effective) / number of patients × 100%) in the experimental group was 90%, and the total effective rate in the control group was 80%. Thus, the difference between the two groups was 10%. We used the calculation formula for superiority trials to calculate the sample size, and the *α* error and *β* error were set at 0.05 and 0.10, respectively. This will require a sample size of 219 participants in each group. The dropout rate is expected to be 20%, which means that a total of 528 patients are needed for the two groups.

This study is an adaptive research study with an interim analysis. In the first stage of the study, 6 hospitals will screen 1/3 of the total sample size, which will be 176 patients. When we calculate the pregnancy rate, the primary outcome of this study, we will go through the first unblinding and interim analysis. The aim of the interim is to find out which of the six diseases are more sensitive to Bushen Culuan Decoction therapy. If Bushen Culuan Decoction shows significant clinical benefit or tends toward a benefit for a certain disease, research on this disease will go into the second stage of the study. If Bushen Culuan Decoction does not reach the treatment effectiveness threshold, research on this disease will be suspended in the next stage. At this time, the sample size will be recalculated according to the interim analysis result.

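### 528 patients do not follow from 219 per group and 20% dropout: they leave about 211 per group, so 528 covers only about 17% dropout

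*Protocol article*

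**What the plan says.** All the figures are in the section on sample size estimation in the protocol article.

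- The assumed total effective rates come from a previous study: "in the experimental group was 90" percent, and "the total effective rate in the control group was 80" percent. The alpha and beta errors "were set at 0.05 and 0.10, respectively".
- The type of calculation is given as follows: "We used the calculation formula for superiority trials to calculate the sample size". Whether alpha is one-sided or two-sided is not stated.
- The size before dropout: "This will require a sample size of 219 participants in each group".
- The size after dropout: "The dropout rate is expected to be 20%, which means that a total of 528 patients are needed for the two groups".

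Allocation is 1:1 (abstract, Methods), so 528 means 264 per group. Two other figures rest on this total: 88 women at each of six hospitals (section on participants; 6 × 88 = 528) and a first stage of 176 (528/3). The same section says that the sample size will be recalculated after the interim analysis.

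**The concern.** A dropout allowance is there to keep the required number of women after the expected losses. Here the plan names a required number, an expected loss and a total to recruit, and the total does not keep the required number at that loss. A reader of the sentence would believe that 20% dropout is fully covered.

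Two things are at stake. One is a small shortfall against the plan's own power target. The other is that the same method could be used again when the sample size is recalculated at the interim, and the shortfall would then pass into the revised number.

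**Working it through.** **Inputs, all from the sample size section except the last.** Rates 0.90 and 0.80; difference 0.10; alpha 0.05; beta 0.10; 219 per group (438 in total); dropout 20%; 528 in total; 1:1 allocation (abstract).

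**Step 1: reproduce 219.** With the average rate p = 0.85 used for both variances and a one-sided alpha of 0.05:

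n = 2 p (1 − p) (z₀.₉₅ + z₀.₉₀)² / d² = 2 × 0.85 × 0.15 × (1.645 + 1.282)² / 0.10² = 218.4, rounded up to 219.

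This matches the plan. With a two-sided alpha, the formulas tried need between 261 and 268 per group, so 219 implies a one-sided 0.05.

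**Step 2: what 528 keeps at 20% dropout.**

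- 528 × (1 − 0.20) = 422.4, or 211.2 per group.
- Against 219 this is about 8 per group too few, a shortfall of 3.6%.

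**Step 3: the dropout that 528 does cover.**

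- 1 − 438/528 = 0.170, or 17.0%.
- Per group: 264 − 219 = 45 losses can be absorbed, whereas 20% of 264 is 52.8.

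**Step 4: the total that 20% dropout requires.**

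- 219 / (1 − 0.20) = 273.75, so 274 per group and 548 in total, 20 more than 528.
- Rounding does not explain the gap: an equal split of at least 548 over six hospitals gives 552 (92 each), not 528.

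**Step 5: where 528 may come from.**

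- 438 × 1.2 = 525.6, so 526. The next multiple of six is 528 = 6 × 88.
- 220 × 1.2 = 264 per group also gives 528.
- Either route multiplies by 1.2. Neither is printed.

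**Step 6: power, by the formula of step 1 (one-sided 0.05).** Power = Φ( d √n / √(2 p (1 − p)) − 1.645 ).

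- n = 219: 0.10 × √(219/0.255) = 2.931; minus 1.645 is 1.286; power 90.1%.
- n = 211: 0.10 × √(211/0.255) = 2.877; minus 1.645 is 1.232; power 89.1%.

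A version with the pooled variance under the null and separate variances under the alternative gives 90.3% and 89.3%. The loss is about 1 percentage point either way.

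**The case against.** Four points can be made on the other side.

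*Dropouts are not removed from the analysis.* The statistical analysis section carries the last observation forward for dropouts, and the withdrawal section keeps their record forms and treats their last results as final. The number analysed therefore need not fall to 211 per group. That is true of the analysis, but it does not rescue the sentence. The plan adds an allowance because it counts dropouts as lost from the 219; if carried-forward women counted in full, no allowance would be needed.

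*The total is provisional.* It will be recalculated after the interim analysis, and some diseases may be suspended. This stands and limits the consequence. It is also the reason to settle the method now.

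*The multiplication is not documented.* This stands. A reader might infer as fact that the authors multiplied where they should have divided. The article prints no inflation formula, so only the mismatch is shown. The shortfall does not depend on how 528 was reached.

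*The shortfall is minor.* This stands too. A reader who assumes a two-sided 0.05 would find about 83.7% power at 219 and 82.3% at 211, and might infer that the dropout step leaves the trial far below 90%. The figures do not support that. On a two-sided basis 219 never gave 90%, so most of that gap exists before any dropout and is a matter of sidedness. That is a separate question, as is the use of a total effective rate when the primary outcome is the pregnancy rate.

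**Conclusion.** The inconsistency is real. As printed, 219 per group, 20% dropout and a total of 528 cannot all hold. At 20% dropout, 528 leaves about 211 per group; it covers 17.0%; and 20% would call for 548.

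The size is small: 8 women per group after dropout, or about 1 percentage point of power (90.1% to 89.1%), which just misses the stated beta of 0.10. The power figures assume the plan's own rates of 90% and 80%, a one-sided alpha of 0.05 (inferred because it reproduces 219), and dropouts counted as lost, as the plan's own allowance treats them.

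A reader might go further and conclude that the trial is seriously underpowered for this reason, or that it must enrol 20 more women. Neither follows from a difference of this size in a total that the plan already intends to revise. The point is a figure to correct and a method to fix before it is used again.

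**What to change.** Restate the dropout sentence in one of two ways:

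- 528 patients keep 219 per group at a dropout of up to about 17%; or
- at 20% dropout, 528 patients leave about 211 evaluable per group, with about 89% power on the basis that gave 219.

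State also that the interim recalculation will obtain the number to recruit as n/(1 − d), where n is the number required and d the expected dropout.

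This is a change of wording and costs nothing. The 88 per hospital and the first stage of 176 can stay, and no extra enrolment is needed. For reference, moving to 548 would mean 3 to 4 more women per hospital (20/6). The trial status section put the end of recruitment at about 20 February 2022, before the article's publication on 8 July 2022, although it still describes recruitment as open, so more enrolment may not be practical in any case.

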### Withdrawal criteria

Participant have the right to withdraw from the study, as defined in the informed consent document, or to “drop out” if they do not explicitly withdraw from the study but are no longer undergoing training and testing. The reason for withdrawal should be understood as far as possible and recorded, for example, perceiving lack of efficacy; intolerance of certain adverse effects; inability to continue the clinical study; and lost to follow-up without explanation. Case record forms for withdrawn participant will be kept, and the results of the last trial will be considered final.

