#### Statistical analysis

An independent statistician will use SPSS 21.0 (SPSS, Chicago, Illinois, USA) to analyze the data.

The mean ± SD will be used to describe normally distributed data, while medians with IQRs will be used if the data are not normally distributed. The *χ*^2^ test will be used for evaluating differences between dichotomous variables, while one-way analysis of variance or Student’s *t* test will be used for evaluating continuous variables. The Mann-Whitney test will be used if the data are not normally distributed. A *p* value < 0.05 will be considered statistically significant.

If there are dropouts from the study, the last-observation-carried-forward principle will be used to compensate for the loss of data.

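### The dropout allowance assumes that women who leave give no outcome, but the analysis keeps them by last observation, so the stated 90% power is not that of the planned analysis

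*Protocol article*

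**What the plan says.** The Sample size estimation section takes a total effective rate of 90% (experimental) and 80% (control) from a previous study. It says "We used the calculation formula for superiority trials to calculate the sample size", with the α and β "error were set at 0.05 and 0.10, respectively". It arrives at 219 per group and then adds for dropout: "The dropout rate is expected to be 20%, which means that a total of 528 patients are needed for the two groups". That is 264 per group.

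The Statistical analysis section gives the rule for women who leave: "If there are dropouts from the study, the last-observation-carried-forward principle will be used to compensate for the loss of data". The Withdrawal criteria section points the same way: "Case record forms for withdrawn participant will be kept, and the results of the last trial will be considered final".

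The Primary outcome section defines the outcome as the pregnancy rate, confirmed by serum β-HCG.

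**The concern.** A dropout allowance replaces women who will supply no outcome. It restores the planned power if those women leave the analysis and the remainder still show the assumed rates. A carried-forward rule does something else: every woman stays in the denominator with her last recorded status. For pregnancy, the last status of a woman who leaves before a positive test is not pregnant. If some of these women would have conceived, both rates fall in proportion, and so does the difference between them.

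The sample size and the analysis therefore rest on different treatments of the same women. This would remain with equal dropout in both arms, with the allowance made by division instead of multiplication, and at either sidedness. At stake is whether the stated β of 0.10 applies to the analysis that will be run, and so how a non-significant result would be read. The sample-size recalculation planned after the interim analysis could carry the mismatch forward.

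**Working it through.** **Inputs.** From Sample size estimation: 90% and 80%, α 0.05, β 0.10, 219 per group, 20% dropout, 528 in total. From the Abstract: 1:1 allocation, so 528/2 = 264 per group. Sidedness is not stated.

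**Step 1: reproduce 219.** With pooled variance, n = (z₀.₉₅ + z₀.₉₀)² × 2 × 0.85 × 0.15 / 0.10² = (1.645 + 1.282)² × 0.255 / 0.01 = 218.4, which rounds up to 219. This is a one-sided 5% level. The same formula two-sided gives 267.9, so 219 implies a one-sided test.

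**Step 2: reproduce 528.** 219 × 1.2 = 262.8, or 263 per group and 526 in total, within two women of 528. The stated total equals six hospitals at 88 each.

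**Step 3: power if dropouts are removed.** 264 × 0.8 = 211 per group at 90% against 80% gives 89.3% one-sided (82.3% two-sided). The one-sided figure is close to the stated 90%, so the allowance roughly does its job under this handling.

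**Step 4: power if dropouts are kept by last observation.** Let f be the share of dropouts' expected pregnancies that is lost. Each rate becomes p × (1 − 0.2f), with all 264 per group analysed. Power = Φ{[Δ√n − z√(2p̄(1−p̄))] / √(p₁(1−p₁) + p₂(1−p₂))}, where Δ = p₁ − p₂ and p̄ is the mean of the two rates.

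| f | Rates | Difference | One-sided | Two-sided |
|---|---|---|---|---|
| 0 | 90.0% / 80.0% | 10.0 points | 94.4% | 89.8% |
| 25% | 85.5% / 76.0% | 9.5 | 87.1% | 79.2% |
| 50% | 81.0% / 72.0% | 9.0 | 78.8% | 68.5% |
| 75% | 76.5% / 68.0% | 8.5 | 70.5% | 58.8% |
| 100% | 72.0% / 64.0% | 8.0 | 62.8% | 50.4% |

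As an example, for f = 100% one-sided: Δ√n = 0.08 × √264 = 1.300; 1.645 × √(2 × 0.68 × 0.32) = 1.085; the denominator is √(0.72 × 0.28 + 0.64 × 0.36) = 0.657; (1.300 − 1.085)/0.657 = 0.327, and Φ(0.327) = 0.628.

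One-sided power falls below 90% once f reaches about 16%. The row f = 0 also covers the case in which the previous study's rates already counted dropouts as failures.

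**Step 5: dependence on the rates.** The article gives no pregnancy rates for planning, so these are assumptions. For 40% against 30%, the Step 1 formula gives 389.7, so 390 per group, and × 1.2 = 468. At full dilution (32% against 24%) one-sided power is 86.1%; at half dilution it is 90.7%. For 30% against 20%, sized the same way, the figures are 87.3% and 91.3%.

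**The case against.** Four points can be made against this.

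*The documents nowhere say that dropouts count as not pregnant.* That is correct. The carried-forward sentence is general and names neither the primary outcome nor an analysis set. The status follows from applying the rule to pregnancy, and only for women who leave before a positive test. The sentence is nevertheless the article's only rule for missing data, and the Withdrawal criteria section agrees with it.

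*Full dilution is extreme.* This stands. A reader might infer that the trial simply has 63% or 50% power. That would require every dropout to leave before conceiving and all her expected pregnancies to go unrecorded. The article has pregnancy recorded through treatment and then every three months, with telephone contact, until pregnancy or 12 months after treatment ends. A woman lost after a positive test is carried forward as pregnant. The range must be shown, with 63% and 50% as its worst end.

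*The inputs are not pregnancy rates.* This also stands. The 90% and 80% are a total effective rate, so the table shows what the plan's own numbers imply and does not forecast power for pregnancy. A reader might infer that extra women can never offset a smaller difference. At lower rates they largely do: at 40% against 30%, half dilution leaves power at about 90%.

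*The earlier rates may already include dropouts as failures.* Their denominator is given only as the number of patients. If so, there is no further dilution and power is 94.4% one-sided. But the 20% allowance would then be unnecessary, and the two sections would still rest on different assumptions.

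**Conclusion.** The point holds as a mismatch of assumptions. The 219 reproduces; the fault lies in pairing a replacement allowance with an analysis that retains dropouts. Unless the previous study's rates already counted dropouts as failures, the stated 90% is not the power of the planned analysis.

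The size is uncertain. On the plan's inputs, one-sided power runs from about 87% down to 63% as the lost share rises from 25% to 100%, assuming 20% dropout in both arms and dropouts who would otherwise have conceived at the planned rates. The two-sided figures are lower partly because 219 was a one-sided number: two-sided power is only 89.8% with no dilution at all. At assumed pregnancy rates of 40% against 30% or below, with the same 10-point difference, the loss is only a few points even at full dilution.

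The documents do not show that the interim recalculation will repeat the mismatch. Rates computed at the interim under the plan's own dropout rule would already be diluted. The risk arises if a separate allowance is again added to undiluted rates.

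**What to change.** In Sample size estimation, compute and restate power on the rates as they will be analysed: all 528 women, with dropouts counted by their last result. Base the figure on pregnancy rates, and give it as a range over the share of dropouts' expected pregnancies assumed lost. State whether the previous study's rates already counted dropouts as failures.

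In the recalculation planned after the interim analysis, use rates computed under the same dropout rule and add no separate dropout allowance.

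This takes a few sentences and needs no extra enrolment. The cost is a stated power that is likely to be less favourable than 90%.

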### Objectives

The objective of this RCT is to evaluate whether Bushen Culuan Decoction enables a higher pregnancy rate than clomiphene citrate in women with anovulatory infertility and to identify the anovulatory diseases for which Bushen Culuan Decoction has higher effectiveness (among AUB-O, PCOS, hyperprolactinemia, LUFS, corpus luteum insufficiency, and POI).

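### Which diseases pass or fail the interim is not evidence that the six diseases respond differently, because the stated rule looks only at the arm difference within each small disease group

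*Protocol article*

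**What the plan says.** The Objectives section makes it a trial aim "to identify the anovulatory diseases for which Bushen Culuan Decoction has higher effectiveness". The Sample size estimation section gives this task to the interim: "The aim of the interim is to find out which of the six diseases are more sensitive to Bushen Culuan Decoction therapy". In stage 1, "6 hospitals will screen 1/3 of the total sample size, which will be 176 patients", and the decision uses the pregnancy rate.

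There are two decision sentences. A disease continues as follows: "If Bushen Culuan Decoction shows significant clinical benefit or tends toward a benefit for a certain disease, research on this disease will go into the" (that is, stage 2). Otherwise: "If Bushen Culuan Decoction does not reach the treatment effectiveness threshold, research on this disease will be suspended in the next stage". The article puts no number on that threshold. The sample size is then recalculated.

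For binary outcomes, the Statistical analysis section says that a χ² "test will be used for evaluating differences between dichotomous variables". Recruitment is balanced by hospital (Participants section); no balance by disease is stated.

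**The concern.** The aim compares diseases with each other. The rule compares the two arms inside one disease at a time, and a tendency is enough to continue. A set of such verdicts will usually be mixed, whether or not the diseases differ.

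Two things depend on this. One is the make-up of stage 2, since a suspended disease recruits no further. The other is the second objective: if the list of continuing and suspended diseases is read as the list of more and less responsive ones, the trial will usually seem to find differences that do not exist. Correcting the final tests for multiplicity would not change that reading.

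**Working it through.** **The plan's own figures.** For 90% vs 80%, β = 0.10 and one-sided α = 0.05 (sidedness is not stated):

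n = [1.645·√(2·0.85·0.15) + 1.282·√(0.9·0.1 + 0.8·0.2)]² / 0.10² ≈ 217 per group, close to the stated 219. Then 438 × 1.2 ≈ 526, and 528 = 6 × 88. One third of 528 is 176, as stated.

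**Inputs for the interim.** 176 women, six diseases and 1:1 allocation come from the article. 176/6 = 29.3 per disease, about 15 per arm, assumes an even mix. The article gives no planning rate for pregnancy (its 90% and 80% are for a total effective rate), so 20–50% is an assumed range. A tendency is modelled first as a higher observed rate.

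**Formula.** With X_T and X_C binomial on 15 women each, q = P(X_T > X_C) by exact enumeration. Over six independent diseases, P(at least one without observed benefit) = 1 − q⁶. If ties also go on, it is 1 − (1 − P(X_T < X_C))⁶.

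| True rates, all six diseases | P(higher) | P(tie) | P(lower) | ≥1 not higher | ≥1 lower |
|---|---|---|---|---|---|
| 30% vs 20% | 0.666 | 0.138 | 0.196 | 91% | 73% |
| 40% vs 30% | 0.651 | 0.129 | 0.220 | 92% | 78% |
| 50% vs 40% | 0.646 | 0.125 | 0.230 | 93% | 79% |
| 90% vs 80% (other endpoint) | 0.698 | 0.155 | 0.146 | 88% | 61% |

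For example, at 40% vs 30%, 0.651⁶ = 0.076 and 1 − 0.076 = 0.924.

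**No effect anywhere (30% vs 30%).** q = 0.421, so at least one disease goes on with probability 1 − 0.579⁶ = 0.96.

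**One responsive disease (50% vs 30%), five null.** The direction rule carries forward exactly that disease with probability 0.830 × 0.579⁵ = 0.05.

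**Precision.** At 40% vs 30%, SE = √[(0.24 + 0.21)/15] = 0.173, so the 95% half-width is 1.96 × 0.173 = 34 points, against a 10-point planning difference. Within one disease, a true 10-point benefit is significant only 7–10% of the time, so the tendency limb decides nearly every case.

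**Other thresholds, common 10-point benefit.** Requiring an observed difference of at least +10 points suspends about 3 of 6 diseases on average. A cut at −10 points suspends at least one in 30% of trials (90% vs 80%), 47% (30% vs 20%) or 55% (40% vs 30%).

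**Other sizes and mixes, direction rule.** With 12 per arm after 20% dropout, at least one disease shows no observed benefit in 92–95%. With an assumed uneven split of 60/40/30/20/16/10 women, 92–94%. With a common 20-point benefit (40% vs 20% or 45% vs 25%), still 63–66%.

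**A confidence-bound rule.** Suspend only if the one-sided 80% upper bound for that disease's difference is at or below zero. At a common 40% vs 30%, at least one disease is then wrongly suspended in about 34% of trials (1 − 0.66^(1/6) ≈ 0.067 per disease) instead of 92%. With partial pooling across diseases, simulation gives about 7–9%.

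**The case against.** **The rule modelled is not quite the rule written.** The suspension sentence names a threshold, and the article defines neither that threshold nor a tendency. The full protocol or analysis plan may do so. This stands: a reader might take 92% as the operating characteristic of this trial's rule, and the documents do not support that. It is the figure for a rule on direction alone. The conclusion survives because no cut tried from −10 to +10 points removes the problem. Likewise, the lack of a stated interaction model or of borrowing is silence that an analysis plan may fill. The point rests on the mismatch between the stated aim and the stated rule.

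**Continuing is not a claim.** A reader might infer that the trial will report passing diseases as responsive and suspended ones as unresponsive. The article says only that a disease enters the second stage or is suspended. A null disease that passes gets more data. Non-pregnant women already enrolled are followed for up to 12 months after treatment (End-of-treatment visit), and the article does not place the interim relative to that follow-up. It is also too strong to call each verdict a coin toss: under a 10-point benefit the direction is right with probability 0.65–0.70.

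**Pooling is not clearly better.** This also stands. Much of the fall in wrongful suspensions comes from the more lenient bound alone (92% to 34%). With one disease truly worse (15% vs 30%) and five at 40% vs 30%, simulation suspends the worse disease in about 29% of trials with pooling, about 56% with the unpooled bound and 89% on direction alone. The choice is a trade-off.

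**Conclusion.** The concern holds in this form: the interim rule cannot deliver its stated aim, and passing or failing it is not evidence that diseases differ in response. Under a common 10-point benefit, at least one disease lacks an observed benefit in about 91–93% of trials (73–79% if ties go on). Under no effect, at least one goes on in about 96%. A lenient −10-point cut still suspends at least one disease in 30–55%. These figures assume an even disease mix and 15 per arm. The pregnancy rates are assumed to be 20–50%, except that the 30% end of the last range uses the article's 90% vs 80%. Smaller or uneven groups make the direction-rule figures slightly worse. The documents do not establish that the trial will publish wrong disease labels, or that hierarchical modelling is required.

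**What to change.** 1. In Statistical analysis and Sample size estimation, state that any conclusion that one disease responds more than another will come only from a treatment-by-disease interaction on pregnancy, with all six disease-specific estimates and intervals shown together, and never from which diseases continued or were suspended.
2. In Sample size estimation, describe the interim as a screen for lack of benefit. Suspend a disease only when a stated confidence bound for its effect excludes benefit, not on the direction of the estimate. Partial pooling across diseases is an option.
3. Report the chances of wrongly suspending and wrongly continuing a disease under the chosen rule, over a range of pregnancy rates and disease mixes.

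The cost is rewording, one extra model and a short simulation, with no extra patients or visits. Three downsides should be stated:
- Fewer unresponsive diseases are dropped at stage 1. An 80% bound nominally suspends a null disease 20% of the time, whereas the strict direction rule fails it 58% of the time (1 − 0.421).
- The interaction test has low power: about 15% on stage 1 data with one disease at +20 points and five at zero, depending somewhat on the form of the test. A non-significant interaction must not be read as equal response.
- Pooling, if used, makes a truly worse disease harder to detect.

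### The sample size is to be recalculated from the same unblinded interim result that selects the diseases; if the observed difference is the input, the new N will usually be too small

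*Protocol article*

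**What the plan says.** All of this stands in the protocol article, Methods, Sample size estimation. The planning rates come from a previous study, where the total effective rate "in the experimental group was 90%, and the total effective rate in the control group was 80" per cent. The article then states "We used the calculation formula for superiority trials to calculate the sample size", with the error rates given as "the *α* error and *β* error were set at 0.05 and 0.10, respectively". The result is "This will require a sample size of 219 participants in each group", raised to 528 in total for 20% dropout.

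One third of that total, 176 women, forms the first stage. Their pregnancy rates are unblinded and compared by disease. If the decoction "shows significant clinical benefit or tends toward a benefit for a certain disease, research on this disease will go into the second stage"; a disease below an effectiveness threshold, for which no value is given, is suspended. The next sentence is "At this time, the sample size will be recalculated according to the interim analysis result".

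The section does not say which interim quantity enters the recalculation, whether N may fall, or whether N is set for the retained diseases together or for each one. Under Statistical analysis, the only test for a binary outcome is a chi-square test at p < 0.05.

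**The concern.** Selection and re-sizing use the same data. Once diseases with an unfavourable observed difference are removed, the average difference in the rest is biased upward. Required N falls with the square of the difference, so an inflated difference gives an N that is too small.

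At stake is the number that justifies the trial. A decoction with exactly the 10-point effect the trial was planned to detect could get a second stage too small to show it. The alternative is a final test that succeeds only because it carries the selection bias forward.

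**Working it through.** **Inputs from the article:** 90% versus 80%, alpha 0.05, beta 0.10, 219 per group, 1:1 allocation, 176 women at the interim, six diseases.

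**Assumptions:**
- Equal disease mix: 176 / 6 / 2 = 14.7, so about 15 per arm per disease; × 0.8 for dropout gives about 12.
- A disease is kept if its observed difference is above 0, as one reading of a trend toward benefit.
- The observed rates of the retained diseases enter the formula.
- The true rates are 90% and 80% in all six diseases.

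**The plan's own figure.** With z = 1.6449 (one-sided 0.05) and 1.2816 (90% power), (1.6449 + 1.2816)² = 8.564.
- Pooled variance: 8.564 × 2 × 0.85 × 0.15 / 0.10² = 218.4, so 219. The figure reproduces as a one-sided calculation.
- Separate variances: 8.564 × (0.09 + 0.16) / 0.10² = 214.1. This form is used below.
- Two-sided, z = 1.96: 10.508 × 0.25 / 0.01 = 262.7, so 263.
- Power at 219 per group: the standard error is √(0.25 / 219) = 0.0338 and 0.10 / 0.0338 = 2.96. Φ(2.96 − 1.645) is about 90% one-sided; Φ(2.96 − 1.96) is about 84% two-sided.

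**Effect of selection** (200,000 simulated first stages, 15 per arm per disease). About 4.2 of the six diseases are kept, and their observed difference averages 16.5 points. By hand, (10 / 16.5)² = 0.367 and 0.367 × 214 = 79, close to the simulated median.

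| One pooled N | One-sided | Two-sided |
|---|---|---|
| N needed per group | 214 | 263 |
| Median recalculated N | 80 | 98 |
| Runs with N below need | 94% | 94% |
| Average power, 15 per arm | 61% | 55% |
| Average power, 12 per arm | 54% | 48% |

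Power is Φ(0.10 / √(0.25 / N) − z), with N at least the stage 1 size already enrolled, for a test that does not profit from the selection.

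**Variations.**
- No disease dropped: average power is 82–84% at 15 per arm. The remaining loss comes from the noise of an interim estimate on about 90 women per arm.
- N set separately for each retained disease: about 57–61% average power per disease. The N values summed over retained diseases exceed 219 per arm in about 89% of runs.
- Stage 1 women pooled into an uncorrected test: rejection is 93–96% one-sided or 88–92% two-sided at 90% versus 80%. With no effect, the same test favours the decoction in about 26% of runs at one-sided 0.05, or 15–16% in the upper tail of a two-sided 0.05 test, where 2.5% is nominal.
- Assumed pregnancy rates of 40% versus 30% (not in the article), 15 per arm: about 48–49% power one-sided and 43% two-sided.

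**The case against.** The strongest reply is that the article never says the observed difference is the input, nor that N may fall. The interim result could mean the number of diseases retained or the control pregnancy rate. The second is plausible, because the planned N rests on a total effective rate and the interim gives the trial its own first pregnancy-rate data. A condensed article may also leave a floor and the method of combining stages to a fuller document. This stands to the extent that the point must be conditional. It does not remove the point: the planned N was itself built by putting observed rates into the formula, and the only interim result described is an unblinded comparison between the groups.

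A reader might infer that the trial will certainly shrink and that its 90% power is lost. The documents do not support that. The Participants section still plans 88 women at each of six hospitals, which is 528. If N is set per disease, as the Objectives could suggest, the total usually exceeds 219 per group, although each disease remains underpowered. Under the only test described, applied to both stages pooled, rejection stays near 90%; the damage is then to type I error, not to power.

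It is also fair that an equal effect in all six diseases is a simplification. If effects differ, retained diseases truly have somewhat larger effects and part of any reduction is legitimate.

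**Conclusion.** The concern holds conditionally. If the observed difference in the retained diseases drives the recalculation, a single pooled N will usually, though not always, be well below what a 10-point difference needs: a median of about 80 against 214 one-sided, and too small in about 94% of runs. The price is either power (about 61% one-sided or 55% two-sided, and about 57–61% per disease if N is set separately) or, with naive pooling of the stages, type I error.

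The size rests on the equal disease mix, the above-0 retention rule and the 90% versus 80% rates. The benchmark needs a caveat too: 219 per group gives 90% power only with a one-sided 0.05 test, and about 84% two-sided. This is a should-fix point, because the published sentence permits the harmful use but does not prescribe it.

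**What to change.** In Sample size estimation, replace the recalculation sentence with a rule on these lines: N is recalculated only from the interim pregnancy rate of both arms together; the planned 10-point difference is held fixed; the observed interim treatment difference is not entered; and N does not fall below 219 evaluable women per group. Say also whether N applies to the retained diseases together or to each one.

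In the scenario above, the floor of 219 alone brings average power to about 91% one-sided or 85% two-sided. It does not cure the type I error of naive pooling, so the text should also say how stage 1 data enter the final test.

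The edit takes a few sentences, and the floor asks for no women beyond those already planned. The trial gives up the chance to shrink when the interim effect looks large. Updating the pooled rate may raise N. With an assumed pooled pregnancy rate of 25%, 8.564 × 2 × 0.25 × 0.75 / 0.01 gives 322 per group one-sided; with 35%, 8.564 × 2 × 0.35 × 0.65 / 0.01 gives 390. The 10 points come from a different endpoint, so the sponsor should confirm that they are also the difference of interest for pregnancy.
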